#### Provisions for ancillary and post-trial care {30}

Patients are carefully monitored until discharge from the hospital and followed-up until four weeks after inclusion. Necessary aftercare is organized by treating physicians independently of this trial. No additional specific ancillary and post-trial care is planned. Despite the efforts of the research team to mitigate risks associated with the intervention, potential small harms may occur. Any potential damage or harm to participants in connection with this trial is covered by the obligatory trial insurance.

### Outcomes {12}

The primary endpoint is time to clinical improvement up to day 28, defined as the time (in days) from randomization to the decrease of at least two levels on the WHO-suggested nine-level ordinal scale (see Table 1) [55] or alive discharge from hospital, whichever occurs first. This standardized primary endpoint allows comparison with other efficacy studies in the context of the treatment of COVID-19.

**Table 1 Tab1:** WHO-Ordinal scale for clinical improvement

Patient state	Descriptor	Score
***Uninfected***	No clinical or virological evidence of infection	0
***Ambulatory***	No limitation of activities	1
	Limitation of activities	2
***Hospitalized: mild disease***	Hospitalized, no oxygen therapy	3
	Oxygen by mask or nasal prongs	4
***Hospitalized: severe disease***	Non-invasive ventilation or high-flow oxygen	5
	Intubation and mechanical ventilation	6
	Ventilation + additional organ support – pressors, RRT, ECMO	7
***Dead***	Death	8

From: WHO R&D Blueprint, Novel Coronavirus COVID-19 Therapeutic Trial Synopsis [55]

*RRT* renal replacement therapy, *ECMO* extracorporeal membrane oxygenation

Key secondary endpoints are:▪ Need for mechanical ventilation, non-invasive ventilation, and intensive care during hospitalization▪ Occurrence of multi organ dysfunction syndrome during hospitalization▪ Number of days requiring oxygen supplementation▪ Change from baseline to discharge of the following biomarkers in patients’ blood samples◦ C-reactive protein (CRP)◦ Neutrophil-lymphocyte ratio◦ Interleukin-6◦ Procalcitonin▪ Change from baseline to follow-up in patient-reported dyspnea, cough, and fatigue on a visual analog scale▪ Patient-reported impact on health by 12-item Short Form Survey version 2 (SF-12v2) at follow-up

Other clinical endpoints include the length of hospital stay until discharge or death (in days) and mortality rate. CRP, interleukin-6, and procalcitonin are measured at baseline, at least every seven days, and at discharge. The safety endpoints adverse events (AEs), including those leading to discontinuation of treatment, serious adverse events (SAEs), and death are also reported.

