### Eligibility criteria {10}

Hospitalized patients with diagnosed COVID-19 are asked to take part in this study when the following eligibility criteria are fulfilled:▪ SARS-CoV-2 infection, verified according to current in-house guidelines▪ High risk for the development of ARDS:i.e., within 24 h before inclusion at least 2 points on an adapted EALI (early acute lung injury) score, with at least one point from the original EALI score [52, 53]Original EALI score:◦ 2–6 l O_2_ supplementation to achieve a SaO_2_ > 90%: 1 point◦ > 6 l O_2_ supplementation to achieve a SaO_2_ > 90%: 2 points◦ Respiratory rate ≥ 30/min: 1 point◦ Immunosuppression: 1 pointModification adapting for risk factors for ARDS in COVID-19 affected patients [54]◦ Arterial hypertension: 1 point◦ Diabetes: 1 point◦ Fever > 39 °C: 1 point▪ Age ≥ 18 years▪ Ability to comply with the inhalation maneuver▪ Ability to understand the clinical trial and sign the informed consent

The presence of any of the following exclusion criteria will lead to exclusion of the patient:▪ Mechanical ventilation or intensive care treatment within current hospitalization▪ Nasal high-flow cannula or continuous positive airway pressure (cPAP) ventilation at time of inclusion▪ Inability to conduct inhalation therapy▪ Hemodynamic instability with requirement of vasopressor therapy▪ Severe comorbidities interfering with the safe participation according to the treating physician▪ Previous participation in this trial, or current participation in another interventional study▪ Pregnancy▪ Systemic immunosuppression for chronic underlying condition (corticosteroid treatment as part of “standard care” allowed)

“Drop-out” is defined as the patient’s withdrawal of consent at any time after inclusion into the study.

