**Fig. 1 Fig1:**
[figure not shown]
Participant timeline. Asterisk symbol (*) indicates the following: if hospital discharge occurs first, intervention is stopped at discharge. Superscript digit one (1) indicates the following: demographics, clinical status according to nine-level ordinal scale, medical history, smoking status, COVID-19 symptoms, and COVID-19 vaccination status. Superscript digit two (2) indicates the following: C-reactive protein, neutrophil-lymphocyte ratio, interleukin-6, and procalcitonin. Superscript digit three (3) indicates the following: on a visual analog scale from 0 to 10. Superscript digit four (4) indicates the following: Clinical status on nine-level ordinal scale, admission to ICU, ventilation, mortality, complications. MRC, Medical Research Council dyspnea scale; SF-12v2, 12-item Short Form Survey version 2

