#### Plans to promote participant retention and complete follow-up {18b}

Patients participating in the study do not receive financial reimbursement. Expenses for the study medication and diagnostics performed only during this study are covered by the study budget. The 28-day follow-up is a phone call, initiated by a study team member at the respective study center. In case of withdrawal of consent or premature termination of the study, data and samples are evaluated in encrypted form until termination of the study.

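### Two key secondary endpoints (ventilation/NIV/intensive care; multi organ dysfunction) have a window that closes at discharge, so faster discharge on aviptadil would shorten observation in that arm

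*Protocol article*

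**What the plan says.** The protocol article, Outcomes {12}, lists among the key secondary endpoints "Need for mechanical ventilation, non-invasive ventilation, and intensive care during hospitalization" and "Occurrence of multi organ dysfunction syndrome during hospitalization". Neither has a fixed day, and the section does not say how a readmission is scored.

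The primary endpoint in the same section has a fixed horizon: "The primary endpoint is time to clinical improvement up to day 28". Its event is a fall of at least two levels on the WHO scale "or alive discharge from hospital, whichever occurs first".

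Contact continues after discharge. Provisions for ancillary and post-trial care {30} states: "Patients are carefully monitored until discharge from the hospital and followed-up until four weeks after inclusion". Plans to promote participant retention and complete follow-up {18b} adds: "The 28-day follow-up is a phone call, initiated by a study team member at the respective study center". A footnote to Fig. 1 lists as collected items "Clinical status on nine-level ordinal scale, admission to ICU, ventilation, mortality, complications". The figure itself is not available to us, so the visits to which the footnote applies cannot be seen.

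Statistical methods {20a} compares binary secondary endpoints by chi-squared or Fisher's exact test.

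**The concern.** A comparison of two proportions is easy to interpret when every patient is observed over the same period. Here the period ends when the patient leaves hospital, and leaving hospital is what the trial hopes to speed up.

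The link is close. The exclusion criteria rule out mechanical ventilation or intensive care in the current stay, and also "Nasal high-flow cannula or continuous positive airway pressure (cPAP) ventilation at time of inclusion". Patients therefore enter at level 3 or 4 of the WHO scale. A fall of two levels from entry lands on level 1 or 2, both of which are ambulatory states. Both routes to the primary event then amount to leaving hospital alive.

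If aviptadil works as assumed, its patients are observed for less time on the two endpoints that show progression. Objectives {7} names the need for mechanical ventilation as part of the secondary objective, and patients are selected for their risk of ARDS. These endpoints should therefore not look better only because observation stopped sooner.

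**Working it through.** **Inputs from the protocol article.** Sample size {14}: hazard ratio 1.75, 80% overall probability of the primary event by day 28, two-sided 5% level, 80% power, 3% drop-out, 132 patients in total. Trial design {8}: 1:1 allocation.

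**The plan's own figure.** n = (1.96 + 0.84)² / (log²(1.75) × 0.25 × 0.8) = 125.17, against 125.2 stated. Rounding up to 126 and dividing by 0.97 gives 129.9, so 130. The next multiple of four is 132. The stated size reproduces.

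**Observation time.** Assumptions, not in the document: time to discharge is exponential, the hazard ratio for clinical improvement applies to discharge, and deaths are ignored.

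- The control hazard λ solves ½[(1 − exp(−28λ)) + (1 − exp(−28 × 1.75λ))] = 0.80, which gives λ = 0.0445 per day. The aviptadil hazard is 1.75λ = 0.0780 per day.
- Discharged by day 28: 71.3% on control and 88.7% on aviptadil (average 80%).
- Mean days in hospital up to day 28 = (1 − exp(−28λ))/λ, which is 16.0 on control. The same formula with 1.75λ gives 11.4 on aviptadil.
- The difference is 4.6 days and the ratio 0.71, so observation is about 29% shorter on aviptadil.
- If 80% is read as the control-arm figure, the means are 13.9 and 9.3 days (ratio 0.67).

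**Events left uncounted.** This step needs an escalation rate, and the document gives none. As an illustration, let the in-hospital hazard h be the same in both arms, with h = −log(1 − 0.20)/28. A patient who stayed in hospital throughout would then have a 20% risk by day 28. After discharge the hazard is r × h. The proportion of patients whose first escalation falls after discharge, and so goes uncounted, is the integral from 0 to 28 of λ·exp(−(λ + h)t)·[1 − exp(−r·h·(28 − t))] dt, with 1.75λ in place of λ for aviptadil.

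| r | Control | Aviptadil | Difference (points) |
|---|---|---|---|
| 0 | 0% | 0% | 0 |
| 0.10 | 0.89% | 1.25% | 0.36 |
| 0.25 | 2.21% | 3.08% | 0.87 |
| 0.50 | 4.33% | 6.03% | 1.70 |
| 1 | 8.31% | 11.56% | 3.25 |

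The last row is a worst case. True risk is 20% in both arms, but the counted risk, h/(h + λ) × [1 − exp(−28(h + λ))], is 11.7% on control and 8.4% on aviptadil. The apparent risk ratio is 0.72 with no drug effect on escalation.

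**The case against.** - **The bias may be negligible.** Patients go home because they have improved, so the hazard after discharge should be well below that in hospital. With 66 patients per arm and a 10% risk, the standard error of a difference in proportions is √(2 × 0.10 × 0.90/66) = 5.2 points, far above the 0.4 points at r = 0.10. This stands as a limit on size. It does not justify a window that depends on treatment when a fixed one is readily available.
- **The bias is conditional.** If discharge times do not differ, the windows match and the test is not distorted. The same rule applies to both arms under blinding. This also stands.
- **Harm after early discharge would be hidden.** A reader might infer this, but the document does not support it. Adverse event reporting and harms {22} collects all adverse and serious adverse events throughout the trial, and mortality in Outcomes {12} is not limited to the stay. An escalation after discharge could appear there. What remains is that it would not clearly enter these two endpoints.
- **A readmitted and ventilated patient is scored as having no event.** A reader might infer this too, but the text does not settle it. The exclusion criteria name the current stay where one stay is meant, and the endpoint wording does not. The ambiguity is itself a reason to clarify, since sites could score the same patient differently.
- **The full protocol, analysis plan or case report form may already cover this.** The Fig. 1 items may be collected at day 28. If so, only the wording needs to change. The article does, however, state a window, and the window it states is the hospital stay.

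**Conclusion.** The point holds, with limits. As written, observation for these two endpoints ends at discharge, which is in practice the primary event, and the planned tests do not allow for unequal observation. Under the plan's own effect size and event probability, with exponential times assumed, mean observation up to day 28 is about 11.4 days on aviptadil against 16.0 on control.

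Any bias from this favors the arm discharged earlier. Its size cannot be fixed from the document. It is nil if nobody escalates after discharge or if discharge times are equal, about 0.4 points at a post-discharge hazard of 10% of the in-hospital hazard, and larger at higher rates. Quoting one figure as the expected bias would claim more than the document supports.

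The primary endpoint, its day-28 horizon, the sample size and the collection of safety data are not affected.

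**What to change.** Define both endpoints as occurring from randomization to day 28, including any readmission. Ascertain them at the day-28 call already planned, if they are not already collected there, and confirm positive answers from hospital records. Keep the in-hospital count as a descriptive result.

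The cost is a wording change to the two endpoints and at most one or two added questions at an existing call. No visit is added and the sample size stays at 132. The small downside is that events after discharge rest on patient report plus a record request. Recruitment is under way (Trial status), so patients already past their call may need a record check. The change should be made while analysts are blinded and before the database is closed.

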#### Intervention description {11a}

Patients in the intervention group inhale 1 ml aviptadil solution (67 μg/ml) three times a day (morning, noon, evening), while participants in the control group inhale 1 ml of NaCl 0.9% three times a day. In both groups, the respective treatment is given in addition to standard care and lasts for 10 days, or until hospital discharge, whichever occurs first. The study drug is administered with the M-neb® dose+mesh nebulizer MN-300/8 in both study groups, and each application will approximately last for 10 min.

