## Statistical methods

### Statistical methods for primary and secondary outcomes {20a}

R will be used for all statistical analyses [59]. Primary and secondary endpoints will be summarized by group using descriptive statistics (mean ± standard deviation for normally distributed data, median and interquartile range for other continuous data, absolute and relative frequencies for categorical data). A log-rank test will be used to compare Kaplan-Meier curves for the primary endpoint “time to clinical improvement,” with failure to reach clinical improvement or death before day 28 being right-censored at day 28. Sensitivity analyses will be performed with “death” and “clinical improvement” as competing risks. For potential confounders that are not fully balanced by randomization, adjusted analyses for the primary outcome may be performed using Cox regression models to estimate hazard ratios with corresponding two-sided 95% confidence intervals to compare with the respective unadjusted Cox model. The proportionality assumption for the Cox proportional hazards models will be tested by assessing Schoenfeld residuals.

Treatment effects on binary secondary endpoints will be analyzed by means of chi-squared test, or Fisher’s exact test, in case expected sub-group size is smaller than five. For discrete secondary endpoints, group differences will be assessed using a Poisson or negative binomial regression, depending on the underlying distribution. Treatment effects on patient-reported severity of symptoms will be analyzed with an ordinal logistic regression and an additional longitudinal analysis with cumulative link mixed models. Effects on longitudinal changes in infection-related biomarkers will be assessed using mixed effect linear regression and analysis of covariance. Patient-reported impact on health at day 28 will be compared between the two groups by means of Student’s *T*-test, or Mann-Whitney-*U* test, depending on normality of the data.

All statistical tests will be performed using two-sided tests at the significance level 0.05. Detailed methodology for statistical analyses of the data collected in this trial is documented in a separate statistical analysis plan (SAP). The SAP is finalized before database closure and can be obtained from the authors upon reasonable request. A summary of the SAP is provided in Additional file 1.

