### Methods in analysis to handle protocol non-adherence and any statistical methods to handle missing data {20c}

The primary analysis will be done in the intention-to-treat population and safety analysis will be done on all patients who started their assigned treatment. The time to clinical improvement will be assessed after all patients will have reached day 28, with failure to reach clinical improvement or death before day 28 considered as right censored at day 28. Careful trial planning and conduct will minimize the occurrence of missing data as far as possible. In case of missing data, treating physicians are contacted with the aim to complete missing data from patients’ records. No data imputation is planned.

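### The biomarker endpoints are read at discharge, a time set by recovery itself, so the between-arm comparison is hard to interpret and tends towards no difference if the drug works

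*Protocol article*

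**What the plan says.** All references are to the protocol article.

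- **Endpoint.** Outcomes {12} lists as key secondary endpoints "Change from baseline to discharge of the following biomarkers": CRP, neutrophil-lymphocyte ratio, interleukin-6 and procalcitonin.
- **Discharge as efficacy event.** The same section ends the primary endpoint at a two-level fall on the WHO scale "or alive discharge from hospital, whichever occurs first".
- **Sampling.** "CRP, interleukin-6, and procalcitonin are measured at baseline, at least every seven days, and at discharge". The neutrophil-lymphocyte ratio is not named in that sentence. The legend of Fig. 1 lists it with the other three, but the figure is not available here.
- **Analysis.** Section {20a}: "Effects on longitudinal changes in infection-related biomarkers will be assessed using mixed effect linear regression and analysis of covariance".
- **Missing values.** Section {20c}: "No data imputation is planned".
- **Exposure and later contact.** Under section {11a}, treatment "lasts for 10 days, or until hospital discharge, whichever occurs first". Under section {18b}, "The 28-day follow-up is a phone call", so that contact gives no blood value at a common time.

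**The concern.** A change from baseline to discharge compares the arms at different study days, and what sets the day is the recovery that the drug is meant to speed. If aviptadil lowers inflammation faster and patients leave sooner as a result, the aviptadil sample is taken early and the placebo sample late. The placebo patient has had extra days to improve, which offsets the drug's effect on the biomarker. The endpoint is also undefined for patients who die in hospital. Outcomes {12} itself treats discharge and death as alternatives when it defines length of stay, and no imputation is planned.

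At stake is the reading of the inflammation results. The introduction rests the rationale largely on anti-inflammatory action, and the discussion expects the secondary endpoints to inform on systemic inflammation markers. A null result on the endpoint as worded could be taken as no anti-inflammatory effect when it may only show that patients in both arms go home at a similar stage of recovery.

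**Working it through.** **1. The plan's own figure.** No figure is given for the biomarkers. The stated sample size reproduces: (1.96 + 0.84)² / (ln(1.75)² × 0.25 × 0.8) = 7.84 / 0.0626 = 125.2. Then 125.2 / 0.97 = 129.04, so 130, and the next multiple of four is 132. After 3% drop-out, 132 × 0.97 = 128, or 64 per arm, which is used below.

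**2. Do sampling times differ by arm under the plan's assumptions?** Ventilation or intensive care in the current stay, and high-flow oxygen or CPAP at inclusion, are exclusions. Entrants therefore start at level 3 or 4 of Table 1, and a two-level fall lands on 1 or 2, both ambulatory. Improvement and leaving hospital are nearly the same event. Assume a constant hazard, with HR 1.75 and 80% improved overall by day 28:

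½[exp(−28λ) + exp(−1.75 × 28λ)] = 0.20, so λ = 0.0445 per day.

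- Median time to improvement: ln 2/λ = 15.6 days on control and ln 2/(1.75λ) = 8.9 days on aviptadil.
- Weibull shapes from 0.8 to 2 give gaps between the medians of about 5 to 7 days.
- Improved by day 7: 1 − exp(−7λ) = 27% on control and 1 − exp(−12.25λ) = 42% on aviptadil.

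**3. What this does to the contrast.** Let the log biomarker fall at slope s, with discharge at time T. The change to discharge is −sT. If the drug multiplies s by k and divides T by k, then (ks)(T/k) = sT and the contrast is zero. If discharge occurs when a fixed level is reached, the change is that level minus baseline and the slope drops out. If T is unrelated to biomarker and drug, the full effect remains.

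The documents give no biomarker variances or discharge rule, so these inputs are assumptions:

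- baseline log-CRP with mean ln 80 and SD 0.7
- control slope 0.15 per day, with lognormal SD 0.3 between patients
- measurement SD 0.4
- stay independent of the biomarker: median 10 days, log-SD 0.4
- discharge level, where one is used: 15

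Arm differences in log units, with two-sided 5% power at 64 per arm:

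| Contrast | Decline 1.25× faster | 1.5× | 1.75× |
|---|---|---|---|
| Fixed day 7 | −0.27 (62%) | −0.55 (99%) | −0.82 (>99%) |
| To discharge, stay unrelated to biomarker and drug | −0.43 (55%) | −0.85 (97%) | −1.27 (>99%) |
| To discharge, biomarker weight 0.5 in timing of stay | −0.19 (26%) | −0.36 (69%) | −0.52 (93%) |
| To discharge, level-triggered, or stay shortened in proportion | about 0 (about 3%) | about 0 (about 3%) | about 0 (about 3%) |

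The last row spans −0.001 to −0.010. The day-7 row can be checked by hand. The mean control slope is 0.15 × exp(0.3²/2) = 0.157, and 0.157 × 7 × 0.5 = 0.55 for the middle column.

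**4. Does the fix work on the scheduled samples?** Take the 1.5-fold case (true day-7 difference −0.55), 2,500 per arm, with samples at baseline, at days 7, 14 and 21 while in hospital, and at discharge. The mixed model has time, time-by-arm, and a random intercept and slope.

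| Discharge timing | ANCOVA of discharge value | Mixed model, day 7 |
|---|---|---|
| Unrelated to biomarker and drug | −0.84 | −0.55 |
| Biomarker weight 0.5 | −0.36 | −0.50 |
| Level-triggered | −0.01 | −0.42 |
| Stay shortened in proportion | −0.01 | −0.56 |

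A separate run at 64 per arm under the same 1.5-fold assumption gave about −0.02 to −0.85 for the ANCOVA and about −0.53 throughout for the mixed model. In either run the mixed model is far less sensitive to how patients are discharged. It is not immune: −0.42 arises where stay depends on the patient's underlying slope, so missing at random does not hold exactly.

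**The case against.** The strongest defence is that the plan is not confined to the discharge value. Outcomes {12} schedules three of the markers "are measured at baseline, at least every seven days, and at discharge", and section {20a} names a mixed model for longitudinal change. That model can compare trajectories by study day. This stands, and it rules out several stronger readings that a reader might infer:

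- **That a real effect is largely cancelled by design.** This needs discharge to follow the biomarker closely. No passage gives a biomarker-based discharge criterion, and the WHO scale rests on oxygen, ventilation and activity. The loss could be nil.
- **That the discharge contrast is the only test of the anti-inflammatory mechanism.** The mixed model is another.
- **That patients who die drop out of the biomarker analysis altogether.** A mixed model keeps their baseline and in-hospital samples. Only the discharge-value analysis loses them.
- **That skewed markers will be analysed untransformed.** A linear mixed model does not exclude log values, and the choice belongs in the analysis plan.

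It is also fair that a fixed-day benchmark is partly unobserved. No sample is scheduled after discharge, so for patients who leave early the day-7 value is a model prediction.

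The defence does not remove the point. The article fixes discharge as the endpoint's time, pairs the mixed model with an analysis of covariance, and names no time-based contrast. On the figures in step 2, many patients may leave before a day-7 sample and have only two values. The sentence on repeat sampling does not name the neutrophil-lymphocyte ratio.

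**Conclusion.** The point holds in limited form. As worded, the endpoint is anchored to a post-randomization time that is part of the primary outcome and is undefined for in-hospital deaths. If the drug works as the sample size assumes, the between-arm comparison of discharge values is not like for like and tends towards no difference. The documents do not fix by how much. Under the assumptions in the working, the 1.5-fold case runs from no loss (power 97%, against 99% at day 7), through a moderate loss (69%), to nearly complete loss (about 3%). The trial's premise, a drug that lowers inflammation and so speeds recovery, points towards the attenuated end but does not establish it. The consequence is confined to secondary endpoints; the primary analysis and the 132 patients are unaffected. It should be corrected because the remedy uses a model and samples that are already planned.

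**What to change.** Define the biomarker endpoint as the treatment-by-time contrast from the planned mixed model, or as its model-based difference at a fixed study day stated in advance. Enter every scheduled sample at its actual study day, including the discharge sample and the samples of patients who later die. State how early discharge and death are handled. Make the change to discharge and its analysis of covariance descriptive. Confirm that the neutrophil-lymphocyte ratio follows the same sampling schedule.

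Cost: no extra samples for CRP, interleukin-6 and procalcitonin. It does change the wording of a key secondary endpoint in a recruiting trial, which may need an amendment and approval under section {25}. For patients discharged early, the fixed-day estimate relies on the model and on missing at random after discharge. The last table in the working shows that this can leave some attenuation, so the assumption should be stated with the result.
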